## Background

Worldwide around 47 million people live with dementia [1] including an estimated 850,000 people in the UK [2]. Services for people with dementia in the UK cost over £17 billion a year, even with savings of around £6 billion a year due to the contribution of family caregivers. In future decades, with an ageing population, increasing numbers of people with dementia are likely to live at home. As in many countries, improving dementia care is a key priority in England [3, 4], with home-oriented care a key objective of the National Dementia Strategy [5]. However, fluctuations in the health and social circumstances of the person with dementia and their family carers may lead to crisis, breakdown in home care and admissions to hospital or long-term care. Focused approaches to manage these problems may sustain care at home, improve quality of life and reduce costs.

Indeed, in one study, one in ten respondents reported a relative with dementia admitted to hospital unnecessarily due to lack of access to community support [2]. For the working age population with mental health problems, Crisis Resolution Teams, designed to avoid inappropriate hospital admission, have shown some reduction in hospital admissions and improvements in patient and caregiver satisfaction [6–10] although requiring better-defined service models [11]. In contrast, people with dementia and their carers experiencing crisis are often supported through a variety of different services varying in nomenclature, staff mix and operational procedure [12]. These services include Community Mental Health Teams, Crisis Resolution and Home Treatment Teams and generic older people’s rapid response teams. All these services are described in this paper as Teams Managing Crises in Dementia (TMCDs). Unlike services for younger adults, there appears to be less evidence and no guidance as to how such teams, or crisis resolution services for older people including those with dementia, should be designed or operate [13, 14].

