#### Random allocation

Following consent, each TMCD will be entered onto a web-based randomisation system and be randomly assigned to one of two arms, either using the Resource Kit or TAU with equal opportunity. The allocation will be determined by a computer-generated pseudo-random code using random permuted blocks of varying size, minimised by the number of people with dementia admitted to psychiatric hospital in the previous 6 months (either classified as low if the number is less than 25, or high if 25 or more) in each TMCD catchment area. The block size will not be disclosed to the research team. The randomisation system was set up and managed by the Research and Innovation team at the University of Nottingham (separate from the research team) in accordance with their standard operating procedure and is held on a secure server. The randomisation process is described in detail in a separate file and held securely within the statistics master file.

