### Sample size

Information collected in different stages of the AQUEDUCT research programme, showed the average hospital admission count per TMCD catchment area over a 6-month period to be between 17 and 33. Following stakeholder consultation, a 20% reduction represented the minimum clinically significant difference in outcome. Therefore, 15 TMCDs will be required in each of the two study arms (30 in total) to detect a 7-point mean admission count difference between arms with 90% power at a two-tailed 0.05 significance level, assuming the count of hospital admissions follows a Poisson distribution. Stata 16 software was used for this power analysis. It is anticipated that no TMCD will withdraw from the study and that NHS Trusts will provide the required hospital admissions data for each TMCD; thus, the number of TMCDs required is unlikely to be influenced by lost information due to withdrawal. However, to manage risk of loss, additional team sites will be kept in reserve.

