### Statistical analysis

The data analysis will be conducted on an intention to treat basis. The treatment effects estimate (95% CI) on the primary outcome and the number of general hospital admissions will be quantified using Poisson regression with binary arm status as an exploratory variable and the size of the population with dementia within each TMCD catchment area as an offset. An over-dispersion check will be performed, and a negative binomial regression model will be used if there is evidence that the outcome variance is greater than the mean. The treatment effect estimates on TMCD practitioners’ and people with dementia and carers’ outcome measures will be explored using multilevel modelling with the TMCD as a level two analytical unit and baseline measures included as covariates [35, 36]. Skewed continuous outcome variables will be transformed for multilevel modelling, and nonlinear multilevel modelling will be performed for categorical outcomes. No interim analysis is planned, and safety and adverse event information will be presented descriptively. Missing values will be imputed via analytical modelling assuming missing at random status. Stata 17 will be used to analyse the data.

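### The population offset fixes the slope on log dementia population at 1; estimating that slope and adding the baseline admission count would cheaply protect power with 30 teams

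*Protocol article*

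**What the plan says.** The Statistical analysis section of the protocol article fixes the model for psychiatric and general hospital admissions: Poisson regression with arm as the only explanatory term and "the size of the population with dementia within each TMCD catchment area as an offset". If over-dispersion is found, "a negative binomial regression model will be used if there is evidence that the outcome variance is greater than the mean". Baseline covariates are named only for the practitioner, patient and carer outcomes.

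Two other parts of the design work on raw counts. Under Random allocation, teams are "minimised by the number of people with dementia admitted to psychiatric hospital in the previous 6 months", cut at 25. Under Sample size, the input is the "average hospital admission count per TMCD catchment area over a 6-month period to be between 17 and 33", Poisson counts are assumed, and "a 20% reduction represented the minimum clinically significant difference in outcome". The same admission counts are also collected for the six months before baseline (Primary outcome measure, and the acute/general admissions outcome).

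**The concern.** I read the offset as log(population), as a Poisson model requires. An offset is a term whose coefficient is set at 1 and not estimated. The model therefore assumes that a catchment with twice the dementia population has, on average, twice the psychiatric admissions, and it takes each population figure as known. The protocol gives no evidence on either assumption. The section on recruiting sites deliberately seeks teams that differ in service model and clientele, which makes a common one-for-one relation less secure, though it does not refute it.

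Any departure that varies between teams enters the team rates at full weight and appears as extra-Poisson variance. With 30 units and a sample size that allows for no between-team variance, this widens the confidence interval of the primary result. It can also cause the over-dispersion that the plan then tests for.

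**Working it through.** **Inputs from the protocol.** 15 teams per arm, two-sided 0.05, 90% power, 7-admission difference, 20% relative reduction, Poisson counts, mean 17 to 33 (Sample size).

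**Assumed inputs, because the protocol gives none.** *b* = true slope of log admissions on log population; *s* = SD of log population, 0.4; *e* = SD of team-specific log error in the denominator; in the simulation also a between-team SD.

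**Step 1: the plan's own figure.** With (1.960 + 1.282)² = 10.507,

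n per arm = 10.507 × (1/m₁ + 1/m₂) / ln(m₁/m₂)².

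For 33 v 26.4 (exactly 20%): 10.507 × 0.0682 / 0.0498 = 14.4, so 15, with power 0.911 at 15. As a comparison of means with difference 7 and SD √33, n is also 15 (power 0.916). The stated 15 reproduces, with almost no slack.

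**Step 2: what a fixed slope adds.** The residual variance of the log rate is

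- offset: v = ((b − 1)s)² + e²
- estimated slope: v = b²s²e² / (s² + e²)

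Put CV² = exp(v) − 1 and add 2·CV² inside the bracket of step 1. Example, b = 0.5 and e = 0 under the offset: v = (0.5 × 0.4)² = 0.04; CV² = 0.0408; bracket = 0.0682 + 0.0816 = 0.1498; n = 10.507 × 0.1498 / 0.0498 = 31.6, so 32. Power at 15 per arm (33 v 26.4):

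| b | e | Offset: power (n for 90%) | Estimated slope: power |
|---|---|---|---|
| 1 | 0 | 0.911 (15) | 0.911 |
| 0.8 | 0 | 0.859 (18) | 0.911 |
| 0.5 | 0 | 0.608 (32) | 0.911 |
| 1 | 0.1 | 0.829 (19) | 0.834 |
| 1 | 0.2 | 0.608 (32) | 0.658 |
| 0.5 | 0.2 | 0.430 (50) | 0.846 |

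Estimating the slope removes the cost of non-proportionality. It removes little of the cost of denominator error when b = 1.

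**Step 3: errors that do no harm.** If every population is wrong by the same factor k, each offset shifts by log k and the intercept absorbs it. The arm effect is unchanged.

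**Step 4: simulation.** 30 teams, mean 25, rate ratio 0.8, allocation stratified at a baseline count of 25, population CV 40%, quasi-Poisson (scale at least 1) with a t reference. Power in %; a dash means no figure is reported here:

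| Setting | Offset | Offset + baseline | Estimated slope | Estimated slope + baseline |
|---|---|---|---|---|
| Slope 1, no error | 74 | – | 73 | – |
| Slope 0.8, error 10% | 63 | – | 71 | – |
| Slope 0.5, no error | 49 | – | 74 | – |
| Slope 1, error 20% | 52 | 51 | 55 | 62 |
| Slope 1, error 20%, team SD 0.2 | 39 | – | 39 | – |
| Slope 0.5, error 20%, team SD 0.2 | 30 | 30 | 47 | 60 |

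Repeat runs of this design differ by a few points (first row: 74 to 78 for the offset, 73 to 76 for the estimated slope). Type I error was about 3 to 5% for both models. The first row lies below 90% because a 20% reduction from 25 is 5 admissions, not 7; by the formula of step 1, 25 v 20 gives 0.82. Only comparisons within a row bear on the offset.

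A negative binomial version at 33 v 26 shows the same pattern. With slope 1 and no error, slope 0.5, error 0.2, and both departures together, the offset gives 0.93, 0.73, 0.65 and 0.48, and the estimated slope 0.92, 0.94, 0.70 and 0.90.

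**The case against.** The outcome is defined by postcode catchment, so a rate per person with dementia is the natural quantity and an offset the usual way to model it. It is far better than ignoring size: at slope 1, no size adjustment gives power 0.27 against 0.91. All of this stands, and it is why the fix keeps the offset.

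The harm is also assumed, not shown. The dementia figure in the Background is national and says nothing about error that differs between catchments, and a slope of 0.5 is a strong choice. Under milder assumptions the difference nearly vanishes: 70% v 69% at slope 1 with 10% error, 69% v 70% at slope 0.9 with 10% error, and 43% v 44% at slope 0.8 with 10% error and team SD 0.2. This stands too, and it limits the claim to a conditional loss. In the most adverse setting, much of the gain comes from the baseline count: with no population term at all it gives 57%. But the baseline count is no general substitute for population. With proportional counts and an exact denominator it gave 0.73 against 0.93 for the offset (33 v 26).

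The unseen analysis plan may add covariates. However, the article states the model and its terms, so this is a comment on a stated choice.

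Three stronger readings are not supported:

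- **That the primary test is invalid.** If plain Poisson were kept despite these departures, type I error would reach 20% (slope 0.5) or 32% (slope 0.5 with error 0.2). The plan provides for a negative binomial model in that case.
- **That any denominator error costs power.** Step 3 shows that a common error does not.
- **That allocating and powering on counts while analysing rates is a contradiction.** It is not; it means only that the sample size never tested the proportionality assumption.

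**Conclusion.** The offset is valid, but it commits the primary analysis to a slope of 1 that the protocol does not support and the power calculation does not use. The possible cost runs from nothing to about 25 points of power from non-proportionality alone (49% v 74% at slope 0.5). Estimating the slope gains nothing where denominator error and between-team variation dominate at slope 1 (39% v 39%). All of these sizes depend on assumed values for slope, denominator error, population spread and team variation, so no single loss can be stated. The case for change rests on asymmetry: the wider model contains the planned one, costs little if the planned one is right, and can recover a material amount if it is not. This is a cheap improvement, not the correction of an error.

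**What to change.** In the primary and general-admission models, keep the log-population offset and add two covariates: log(dementia population), so that its slope is estimated, and the log of that outcome's own baseline six-month count. With the offset retained, a coefficient of 0 on log population corresponds to the planned model, and the arm effect remains a rate ratio. Make both additions together. Estimating the slope alone repairs little of the denominator error, and adding the baseline count with the slope still fixed gains little when the denominator is in error. Report the offset-only model as a sensitivity analysis, and settle the wording before unblinding.

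Cost: analysis-plan wording only, because the populations are already needed and the baseline counts already collected. The downside is 1 to 2 degrees of freedom with 30 teams, or about 1 to 4 points of power if proportionality and the denominator are both exact and teams do not otherwise vary.

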#### Economic evaluation

A cost-consequences analysis will be undertaken, laying out a specified list of costs, including Resource Kit costs, service use and trial outcomes (hospital admissions and quality of life measures). Bootstrapping will be used to generate incremental cost-effectiveness ratios and plot cost-effectiveness acceptability curves. A cost-effectiveness analysis will be undertaken, examining Resource Kit costs and secondary care use costs (using national unit cost measures) and comparing these with changes in the primary outcome measure. Sensitivity analyses will be conducted to assess the implications of variations in team staff case-mix upon outcomes.

The primary economic evaluation will be a cost-utility analysis from an NHS perspective based on the within-trial period. The incremental cost per QALY (quality-adjusted life year) gained for the Resource Kit versus TAU will be calculated for the average TMCD. QALYs gained will be estimated as the number of weeks multiplied by the utility of observed survival for patients and carers within the average TMCD. The utility values will be estimated from the EQ-5D-5 L health status questionnaire [27], completed at follow-up and the associated published societal utility tariffs.

An economic analysis plan will be approved by the DMC before data are accessed. Statistical methods, such as accounting for missing data and adjustment will be consistent with the statistical analysis plan.

### Qualitative aspects of trial

To enhance understanding of participants’ experience of and engagement with the intervention the trial includes a qualitative component. Study-specific questionnaires will be completed by 45 TMCD practitioners from the intervention arm of the trial (three practitioners per team), and researchers will conduct semi-structured interviews remotely, via telephone or multimedia, with 12 people with dementia or their carers who received input within the previous 6 weeks from a TMCD in the intervention arm.

Both thematic and narrative analysis of interview transcripts will be deployed to identify experiences both of staff providing the intervention and of people with dementia and their carers receiving it. At least two researchers will review each transcript to increase trustworthiness. Once all aspects are coded, key themes and processes will be identified through a process of conceptual abstraction. The point of reaching thematic saturation [37] will be agreed with members of the wider research team.

## Discussion

The AQUEDUCT programme is designed to address the better management of crises in the care of people with dementia. The trial is built upon knowledge gaps identified in previous work by team members [16, 19] and has involved literature reviews [12], the development of practice modules for service improvement [14, 20], and a feasibility study [23].

There is limited evidence for the precise content of crisis resolution services for people with dementia and their effectiveness and cost-effectiveness. Nonetheless, people with dementia and carers value a coordinated and well-focused approach to addressing crises in their care [15]. Policy in dementia care continues to emphasise the importance of care at home and of avoiding unnecessary admissions to hospital care [3–5, 38]. There is therefore a need for more precise evidence of the form and content of an improved model of crisis services for people with dementia and their carers.

Health and social care services need to better understand what interventions prevent hospitalisation and enhance well-being for people with dementia and carers in the period leading up to or during a crisis. This trial can contribute to such a knowledge base if the intervention proves to be clinically and cost-effective. It is hypothesised that a more precise model of crisis management, supported through provision of a Resource Kit, can reduce admissions to hospital and improve the well-being of people with dementia and their carers.

This study could have wide-ranging value in improving crisis management for people with dementia and their carers and evidencing what works for service commissioners and planners, health and social care professionals, and researchers both nationally and internationally. Evidence from this study will be submitted for publication in peer-reviewed journals and findings presented at relevant conferences and events. To achieve impact, the Resource Kit will be made available after the trial has ended, as part of our programme of implementation and dissemination.

### Trial status

The trial is due to commence recruitment in July 2021 and will continue until November 2022.

## Data Availability

The study datasets are available from the CI on reasonable request.

## Abbreviations

AQUEDUCT: Achieving Quality and Effectiveness in Dementia Using Crisis Teams
CI: Chief Investigator ([name])
CONSORT: Consolidated Standards of Reporting Trials
COVID-19: (Novel) Coronavirus disease 2019 (WHO nomenclature)
CSQ-8: Client Satisfaction Questionnaire – 8 item version
DMC: Data Monitoring Committee
EQ-5D-5 L: EuroQoL quality of life questionnaire – 5 + 5 item version
GHQ-12: General Health Questionnaire – 12 item version
NHS: National Health Service
NIHR: National Institute for Health Research
PPI: Patient and public involvement
QALY: Quality-adjusted life year
REDCap: Research Electronic Data Capture
SPIRIT: Standard Protocol Items: Recommendations for Intervention Trials
TAU: Treatment as usual
TMCD: Team Managing Crisis in Dementia
TMCDs: Teams Managing Crisis in Dementia
TMG: Trial Management Group
TSG: Trial Steering Group
UWES: Utrecht Work Engagement Scale
WAAQ: Work Acceptance and Action Questionnaire
